### Recruitment

Several strategies will be applied to recruit participants. In this RCT, we will recruit participants both from the pediatric inpatient and outpatient departments of Dongguan Kanghua Hospital. We will advertise in public areas of the hospital and through media such as WeChat (a Chinese multipurpose social media mobile application software), which will provide brief descriptions of the eligible population as well as the purpose, procedures, interventions, possible risks of the trial, and contact information for the researchers. After eligibility assessment, the guardians of all eligible patients will be requested to sign informed consent forms. Clinical recruitment staff will be responsible for the recruitment process.

### Randomization and allocation concealment

Eligible patients will be allocated by research staff according to a computer-generated random sequence in a 1:1 ratio to the two groups (*Tuina* or sham *Tuina*) of the study. Random allocation will be generated by means of sealed envelopes by the independent statistician and will not available to any member of the research team until the databases are completed and locked. According to the random number table, allocations to the two groups will be assigned and coded by persons who are not involved in the clinical trial and will then be placed in sealed opaque envelopes with sequence numbers also containing the group assignment and type of intervention. When new participants are enrolled in the study, the *Tuina* therapists will open the envelopes in sequence and assign participants to the relevant intervention accordingly. All processes will be recorded and saved as appropriate.

### Blinding

In this study, patients, caregivers, research staff, outcome assessors and data statisticians will be masked to assignment. However, *Tuina* therapists cannot be masked as sham *Tuina* will be practiced differently from real *Tuina*. Participants will be assigned to receive their corresponding interventions in separate rooms to avoid communication. *Tuina* therapists will not be allowed to share any information in terms of patient intervention with other researchers, including outcome assessors and data statisticians. Furthermore, therapists are prohibited from speaking with guardians or participants about group allocation information. To ensure successful blinding implementation, therapists will perform manipulations under an opaque cloak-shaped device, big enough to cover the upper body and arms of a child who is 6 years old or younger. Two narrow holes are present for therapists to insert their hands through and perform *Tuina*. The entire manipulation process will be covered by the cloak. In addition, the outcome assessors who are not aware of what kind of treatment the children received will ask the participant’s guardian to complete the questionnaire independently in a separate room during the intervention as well as the follow-up period and will not be allowed to directly communicate with the therapists during the whole study process.

### Data collection

In this study, two data collectors will be responsible for collecting all data when the children are recruited. A printed case report form (CRF) with a three-digit identification number for each participant and electronic follow-up questionnaires will be used to record all information. Each participant will have a unique three-digit identification number that will be pre-recorded on the printed CRF. The social demographic characteristics of the participants including age, height, weight, medication history and present condition will be collected. Clinical outcomes will also be collected by outcome measurement instruments during the entire intervention and follow-up period. Participants will be appropriately compensated if they complete the entire procedure. During the intervention and follow-up period, electronic questionnaires will be sent to the participant’s guardian through WeChat. For those guardians who do not have a WeChat account, telephone surveys will be used to fill in printed questionnaires which contain the same information as the electronic version. All electronic information obtained through WeChat will be recorded on reserved sections in the CRF. AEs, if any, will also be recorded. Participants have the right to withdraw from the study at any time, for any reason.

### Data management

CRFs completed in Dongguan Kanghua Hospital will be sent to the research office based in the 2nd Affiliated Hospital of Guangzhou University of Chinese Medicine. A data administrator will be responsible for checking the completeness and logicality of the data. Afterwards, double entry will be performed independently by two team members, and accuracy will be checked using point-by-point comparison with the original data. The data manager and the trial statisticians will have the right to access the final trial dataset.

### Statistical analysis

Statistical analysis will be performed by trial statisticians who are blinded to the group allocation using SPSS Statistics Software 19.0 and SAS version 9.4. All statistical tests will be two sided with a significance level of 0.05. We will summarize the social demographic characteristics of the participants by groups using simple descriptive statistics. Normally distributed quantitative variables will be described by means and standard deviation and non-normally distributed variables will be described by median and interquartile range. In addition, the 95% confidence intervals will be presented when calculating the difference in means between groups. For categorical variables, numbers and percentages will be presented.

We intend to use the intention-to-treat and per-protocol approach to analyze data. For intention-to-treat analysis, all participants will be included in the analysis according to the group to which they were originally randomized, regardless of whether they complete the treatment or adhere to the protocol. For per-protocol analysis, only participants who complete the whole treatment (i.e., those who receive treatments once per day for 3 consecutive days) will be included. Between-group comparisons will be performed using two-sample *t* tests for normally distributed data and Mann–Whitney *U* test for non-normally distributed data. For categorical variables, chi-square tests or Fisher’s exact test will be used for group comparison.

Multivariable regression analysis will be performed to analyze the associations between pediatric *Tuina* and primary or secondary outcomes with adjustment for covariates including social demographic characteristics, birth characteristics, medication history, and so forth. Missing data will be imputed through multiple imputation using chained equations.

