### Participants

The participants will be recruited from Dongguan Kanghua Hospital in Guangdong province, China. All participants will complete a screening form to assess their eligibility. This study will enroll 122 children with acute diarrhea. The diagnosis of diarrhea will be based on criteria as identified by Shen and Wang [27] and the WHO [28].

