#### Primary outcomes

The primary outcome measure for diarrhea will be diarrhea days from baseline and diarrhea times on the third day. The assessment of diarrhea days refers to the period of days from baseline to the first day that diarrhea is reduced to less than or equal to two times per day throughout the treatment and follow-up period. Diarrhea times will be evaluated on the third day of intervention. In this study, we define the baseline and the first day of intervention as the same day.

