### Sample size estimation

This study includes two primary outcomes: diarrhea days and diarrhea times. Sample size was estimated based on the two primary outcome measures. Estimation according to diarrhea days was based on results from previous relevant literature [29], which established diarrhea days in children as 2.1 days after receiving *Tuina* plus usual care. The estimated standard deviation is 1.4. Diarrhea days in children after receiving usual care is 4.0 and the estimated standard deviation is 3.5. On the basis of a 5% false-positive error rate (α = 0.05, two-sided) and 90% power (β = 0.1), sample size was estimated using PASS11 software. A sample size of at least 35 participants should be recruited in each group. Assuming an approximate 20% dropout rate, a total of 84 (70 plus 20% is 84) participants should be enrolled in the trial (42 in each group).

Estimation according to diarrhea times was likewise based on reference from previous relevant studies [30], which established diarrhea times in children as 4.1 times per day after receiving *Tuina* plus usual care. The estimated standard deviation is 1.5. Diarrhea times of children after receiving usual care is 6.2 times per day and the estimated standard deviation is 4.8. On the basis of a 5% false-positive error rate (α = 0.05, two-sided) and 90% power (β = 0.1), sample size was estimated using PASS11. A sample size of at least 51 participants should be recruited in each group. Assuming an approximate 20% dropout rate, a total of 122 (102 plus 20% is 122) participants should be enrolled in the trial (61 in each group).

Based on these results, we chose the larger number sample size, that is 122 participants, for the estimated final trial sample size.

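### Day-3 diarrhea times is compared without adjustment for pre-treatment stool frequency, which the covariate list does not name; the cost is precision only, and its size depends on a correlation the protocol does not give

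*Protocol article*

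**What the plan says.** All references are to the protocol article.

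- Primary outcomes: "Diarrhea times will be evaluated on the third day of intervention". The outcome is the raw count on that day, not a change from entry. The same section treats baseline and the first day of intervention as one day.
- Statistical analysis, test: "Between-group comparisons will be performed using two-sample *t* tests for normally distributed data and Mann–Whitney *U* test for non-normally distributed data". Neither test uses a baseline value.
- Statistical analysis, regression: a multivariable regression of the primary or secondary outcomes is added, with "adjustment for covariates including social demographic characteristics, birth characteristics, medication history, and so forth". The list is open-ended, and the section does not say whether the test or the regression leads.
- Inclusion criteria and Participants: a child must have at least five stools a day, with onset within 72 hours, and "All participants will complete a screening form to assess their eligibility".
- Data collection: "The social demographic characteristics of the participants including age, height, weight, medication history and present condition will be collected". A stool count is not itemised.
- Randomization and allocation concealment: children are allocated "according to a computer-generated random sequence in a 1:1 ratio to the two groups". No stratification is described.

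**The concern.** The pre-treatment value of an outcome is usually one of its better predictors. Here it has to be established before entry, yet the stated comparison ignores it and the regression names birth characteristics while leaving it unnamed. If starting frequency predicts the day-3 count within arms, the variation it explains stays in the error term. A chance difference between arms in starting frequency then moves the observed day-3 difference in proportion to the within-arm slope.

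The point matters more for this outcome than for diarrhea days. Diarrhea times sets the total of 122, and on the article's own inputs it has the lower power of the two primary outcomes.

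**Working it through.** **Inputs** (Sample size estimation). Diarrhea times: the cited source is one "which established diarrhea times in children as 4.1 times per day after receiving *Tuina* plus usual care", with SD 1.5; usual care 6.2, SD 4.8. Diarrhea days: 2.1 (SD 1.4) against 4.0 (SD 3.5). Error rates: "On the basis of a 5% false-positive error rate (α = 0.05, two-sided) and 90% power (β = 0.1), sample size was estimated using PASS11". Stated need for diarrhea times: 51 per group, raised to 122 in total for 20% dropout.

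**Step 1: the stated figure.** The difference is 6.2 − 4.1 = 2.1 and the variances sum to 1.5² + 4.8² = 25.29. The two-sided normal formula gives n = (1.960 + 1.282)² × 25.29 / 2.1² = 60.3, so 61 per group; the unequal-variance t test needs 62. The stated 51 is not reproduced two-sided. A one-sided 5% test gives 50 (normal) or 51 (unequal-variance t).

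**Step 2: unadjusted power.** At 51 per group, SE = √(25.29/51) = 0.704, noncentrality = 2.1/0.704 = 2.98, df ≈ 59.7, two-sided power 83.5%. For diarrhea days the same calculation gives 94.4%. At 49 per group (122 × 0.8 / 2 = 48.8) the figures are 82.0% and 93.5%.

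**Step 3: adjusted power.** The correlation r between pre-treatment and day-3 counts is not in the document, so 0.2 to 0.5 is an assumed range. Two definitions of r give slightly different answers.

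(a) r is the pooled within-arm correlation. Residual variance is multiplied by 1 − r².

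(b) r is the same in each arm and one common slope is fitted. The arm slopes, per SD of baseline, are 1.5r and 4.8r, and their average is 3.15r. The mean variance of 25.29/2 = 12.645 falls by (3.15r)² = 9.92r², a reduction of 0.785r².

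| r | (a) variance reduction | (a) power, 51 per group | (b) variance reduction | (b) power, 51 per group |
|---|---|---|---|---|
| 0 | 0% | 83.5% | 0% | 83.5% |
| 0.2 | 4% | 85.0% | 3% | 84.7% |
| 0.3 | 9% | 86.8% | 7% | 86.1% |
| 0.4 | 16% | 89.3% | 13% | 88.1% |
| 0.5 | 25% | 92.3% | 20% | 90.6% |

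At 49 per group, definition (a) gives 83.5%, 85.4%, 88.0% and 91.3% for r = 0.2 to 0.5. A simulation of the adjusted model with robust standard errors at 49 per group gave about 85% at r = 0.3 and 90% at r = 0.5.

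**Step 4: equivalent sample size.** Under (a) the gain equals 1/(1 − r²) − 1 more patients: 4%, 10%, 19% and 33% at r = 0.2, 0.3, 0.4 and 0.5.

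**The case against.** The strongest reply is that the covariate list is illustrative. Data collection places present condition among the social demographic characteristics, and that could cover current stool frequency. An adjusted analysis of the primary outcomes is planned, and the final covariate list is often left to an analysis plan that is not shown. This stands in part: the baseline count is unnamed, and a reader who infers that it is excluded goes beyond the text. It does not remove the point, because the between-group test that the article does state is unadjusted.

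Other stronger readings are tempting and are not supported:

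- *The day-3 comparison is biased.* Allocation is randomized, so it is not. Nor does a baseline imbalance pass in full into the result; it carries over only in proportion to the slope.
- *Age goes unused.* Data collection lists age among the social demographic characteristics, which the regression includes.
- *The count and the hours since onset are already on file.* Eligibility needs only a threshold for each, and a yes/no entry would satisfy it. Recording of the actual values is an inference.
- *The 83.5% results from not adjusting.* The shortfall from 90% comes mainly from the sample size, which matches a one-sided test (Step 1). That is a separate matter. With all 61 per group evaluable, unadjusted power would be 89.6%.
- *The absence of stratification is an error.* It is not one at this size, and an article may leave such detail out.

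The entry floor of five stools narrows the baseline range and may lower the correlation. This also stands, and it is why small values belong in the range.

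**Conclusion.** The concern holds as a loss of precision on one primary outcome. The stated test for day-3 diarrhea times leaves out a predictor that must be ascertained before entry, and the regression list does not secure its use. The size rests on an assumed correlation: about 1 to 1.5 points of power at 0.2, about 3 at 0.3, and 7 to 9 at 0.5, starting from 83.5% at 51 per group. Below about 0.3 the benefit is small, though one prespecified covariate then costs almost nothing. The calculation also takes the planning means and SDs as given and assumes a roughly linear relation. Validity of the unadjusted comparison is not in question.

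**What to change.** Make the primary analysis of day-3 diarrhea times a linear model with robust variance on treatment and pre-treatment stool frequency. Define the covariate as the screening count taken before the first session, because baseline and the first treatment day coincide. Robust variance suits the very different planning SDs (1.5 and 4.8). State this model as primary, fix it before unblinding, and report the unadjusted difference as support. Replace the open end of the covariate list with a closed one. Age is already covered; time since onset may be added if it was recorded.

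The cost is wording plus one check: that the screening form or case report form holds the actual count. Recruitment began in January 2017 and the current version is dated April 2019, so a count that was not recorded cannot be supplied by a change of text. In that case the unadjusted comparison remains valid.

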### Adverse event management

During the study period, all adverse events experienced by the participant throughout the treatment and follow-up periods, regardless of relevance to the interventions, will be documented and immediately reported to the Ethics Committee. The time of occurrence, severity, duration and treatment of AEs will be documented on the AE report form and dealt with using appropriate treatment methods. Potential AEs include local skin damage and rash. The Principle Investigator will supervise the handing of AEs and ensure that adequate action has been taken.

## Ethics and dissemination

### Protocol amendments

Any important protocol amendments will be submitted to the Ethics Committee for approval. After approval, an update will be made to ClinicalTrials.gov.

### Consent or assent

The study has been approved by both Ethics Committees based in Guangdong Provincial Hospital of Chinese Medicine as well as in Dongguan Kanghua Hospital. Written informed consent will be obtained from the guardians or parents of all trial participants by trained investigators. Additionally, oral informed consent will also be obtained when the children are between 3 and 6 years of age. The investigators will explain the nature of the study, purpose, potential risks and benefits in detail to each participant and their guardians or parents. After the participants’ guardians have read and understood the nature of the study, they will be provided with adequate time to decide whether or not to participate. The participants and their guardians have the right to refuse to join the study or to withdraw from the study at any time during the study. Their decision will not affect subsequent medical assistance and treatment.

### Ancillary and post-trial care

If patients experience adverse events during the trial, a medical expert committee will determine if it is related to the trial. The medical expert committee includes members from the Ethics Committee of Guangdong Provincial Hospital of Chinese Medicine, members from the Ethics Committee of Dongguan Kanghua Hospital, and the Principle Investigator. Researchers will provide the cost of treatment and financial compensation for experiment-related harm according to guidance from the Good Clinical Practice Act.

### Dissemination policy

Both positive and negative trial results will be disseminated in several ways. They will be presented at key international conferences, published in peer-reviewed and high-ranking journals, made available on specialist websites, disseminated by the Pediatric *Tuina* Committee, and provided as feedback to patients or professionals by holding *Tuina* workshops or seminars.

## Discussion

The current study is designed to evaluate the efficacy of pediatric *Tuina* for children with acute diarrhea. A series of trial feasibility criteria have been established. If all criteria are met, the trial will be considered feasible. If they are not met, and revisions are not possible, the trial will be considered unfeasible. Where the trial is considered unfeasible, and revisions are possible, details of suggested revisions will be described in feasibility trial outputs. Feasibility criteria have been established as follows: 1) recruitment is feasible, indicated by randomization of the targeted population; 2) treatment and attendance are acceptable, indicated by attending more than 67% of the anticipated three sessions offered; 3) data collection procedures are feasible, indicated by sessions recorded; 4) missing data are at an acceptable level, indicated by 80% of visits completed and minimal noncompletion of within-visit questionnaires; and 5) estimates needed for sample size calculation are obtainable.

We anticipate two main challenges to be overcome in this study. The first challenge is how to choose a reasonable comparison. In previous studies, researchers often chose the following interventions for the control group [31–35]: 1) standard/usual care; 2) sham/placebo massage, meaning gentle, still touch producing no indentation in the skin; 3) therapeutic touch from the west; 4) special TCM treatments, including acupuncture, Chinese herbal medicine, cupping and so on; 5) blank control; and 6) other controls. In clinical trials based on evidence-based medicine, validation of treatment modalities has invariably adopted the procedures of randomization and placebo-controlled designs [36]. However, the development of placebo controls has been a unique challenge in evaluating the specific benefits of *Tuina*. Ideally, to exclude the potential placebo effect, participants should not know whether they are receiving true or sham intervention treatment in double-blind, controlled clinical trials [37].

In recent years, some researchers have used sham massage (gentle, still touch producing no indentation in the skin) as control treatment in clinical trials and showed that this gentle, still touch was ineffective [38]. Although this method improves the quality of study, there are still some disadvantages for older children who have previously experienced pediatric *Tuina*, particularly in clinical trials of blind design. Specifically, those children and their guardians who are familiar with *Tuina* may be skeptical about the manipulation received and hinder the validity of blinding. In our study, we use a cloak-shaped device to cover the upper body and arms of the child. Sham *Tuina* manipulation consists of the therapist using one hand to hold the child’s hand or putting one hand on the child’s body while the other hand performs manipulations under the cloak on the therapist’s own hand instead of the child’s hand or body. In addition, we only include children who are under 6 years old and exclude children who have a history of experiencing Chinese pediatric *Tuina* on the hands. Therefore, this design can avoid previous limitations in other research.

The second challenge is the implementation of the blinding method. The use of blinding is regarded as an important criterion to evaluate the methodological quality of clinical trials [39]. Due to the characteristics of pediatric *Tuina* and the particularity of operation, it is difficult to design double-blind clinical trials. Therefore, most studies are designed as open trials. Although a few studies used the blind method in clinical trials, treatment assignment was only masked to the outcome assessor and/or investigator. Some studies made use of a privacy screen, where massage was performed behind the screen to maintain “masking” of the infant’s group assignment to parents and newborn intensive care unit clinical staff [40]. However, *Tuina* can be difficult to perform on younger children without the presence of their guardian. We designed a cloak-shaped device to blind the children’s guardians. The cloak covers the child’s hands and upper body and all manipulations will be performed under the cloak. As a result, guardians can be blinded and present during treatment. This type of blinding can make up for the deficiency of previous studies.

To reduce possible bias and improve the quality of study, the following methods will be adopted. First, this study is designed as a randomized, double-blinded trial. Randomized methods and allocation concealment will be performed according to a standardized procedure. Except for the *Tuina* therapists, all patients, caregivers, study staff, outcome assessors and data statisticians will be masked. Second, this study will use a sham *Tuina* method as a control and a specifically designed cloak-shaped device to cover the upper body of a child for the purpose of blinding. This method is pioneering in a clinical study. Third, *Tuina* therapists, data collectors and outcome assessors will participate in training before the trial commences. All operating procedures including *Tuina* manipulation, acupoint selection and outcome assessment will be carried out strictly according to the standardized methods.

In conclusion, this protocol provides a standardized process to guide subsequent clinical research. We expect the trial to demonstrate the efficacy of *Tuina* therapy for the treatment of acute diarrhea. The results of this trial will help doctors have a deeper understanding of *Tuina* therapy and will provide valuable evidence for future research in this area.

